#### Preliminary data analysis plan

4.1.1

Given the relationship between cardiorespiratory fitness and mortality [69], we will conduct the primary analysis on changes in fitness. First, to ensure successful randomization, the two groups will be examined for homogeneity. If it is determined that the groups differ significantly on any variable, we will include those variables as covariates in subsequent analyses. For the primary outcome (VO_2peak_), we will apply intention-to-treat (ITT) principles with all available data included in the first set of analyses [70,71], with the assumption that participants who are lost to follow-up will not have changed their level of fitness since their last observation.

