### Overview

2.1

The currently proposed study is a community-based, pragmatic randomized-controlled trial. The aims of this study are to 1) test the impact of PlayFit, compared to Small Team Training (STT; i.e., group exercise), on cardiorespiratory fitness (i.e., VO_2peak_) and moderate-to vigorous-intensity physical activity (MVPA; self-reported and objectively monitored) after 6-and 12-months, and 2) examine group differences in rates of injury and PA program enjoyment and changes in self-efficacy, blood pressure, loneliness, anxiety, and depression. We hypothesize that participants randomized to both groups will improve their cardiorespiratory fitness similarly at month-6 (i.e., approximately 3.5 ml/kg/min), but those randomized to PlayFit will maintain these increases at month-12 through better attendance. Additionally, we hypothesize that changes in group attendance and cardiorespiratory fitness at month-12 will be mediated by group enjoyment. Finally, we hypothesize that participants randomized to PlayFit will demonstrate greater improvements in indices of physical health (i.e., blood pressure) and mental health-related (i.e., anxiety) outcomes compared to STT while reporting similar injury rates. All study procedures presented here have been approved by the Institutional Review Board (IRB).

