### Covariates and other variables

2.5

PA **program satisfaction.** Satisfaction for the assigned group (i.e., net promoter score) will be measured at the end of each month using the question: “How likely are you to recommend this program to a friend?” using a 10-point (0 = Not at all likely, 10 = Extremely likely) scale. This single-item question has shown to be predictive of future sales growth in marketing studies [57]. In addition, we developed several face-valid questions to measure anticipatory enjoyment, including 1) “How much, if at all, do you look forward to the exercise sessions?” (0 = Not at all, 4 = Very much), 2) “Have you gotten together, outside of these exercise classes, with someone you met in this program?”, and three open-ended items including 1) "What's the one thing we could do to improve the exercise program?”, 2) "What's the one thing you like best about the exercise program?”, 3) “In one sentence, how would you describe what these exercise sessions are like, if a friend asked you.” A final question will also be posed to the participant to rate the exercise leader who led their most recently attended session, “How would you rate this instructor?” (0 = Poor, 4 = Excellent).

**Exercise self-efficacy.** Exercise self-efficacy will be measured using the 5-item self-efficacy scale developed by Marcus and colleagues [58]. Other studies have reported good internal consistency (Cronbach's *α* = 0.76) and test-retest reliability over a 2-week period (*r =* 0.90) [7].

**Preference for exercising in groups versus alone.** This 4-item measure has been used to assess the preference of adults for exercising alone versus in groups, and in different age groups [59], on a 5-point Likert-type scale ranging from −2 (Very unappealing) to + 2 (Very appealing).

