### Randomization

3.2

Following the baseline exercise visit and accelerometer wear period (see Fig. 1), participants will be radnomly assigned using stratified assignment by age (i.e., those over and under 35 years of age) and biological sex. The randomization will be performed using REDCap software. Following randomization, a research staff member will contact the participants to review their exercise group assignment, where the sessions will be held, what they should bring to each session, and answer any additional questions. Additionally, participants will be given the option to install a smartphone application to receive session confirmations and, if necessary, cancellation notifications from the PA program leaders.

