#### Analysis of main outcome: fitness changes

4.1.3

To conduct these analyses using the principles of ITT, a slope will be fitted for the outcome variable (i.e., VO_2peak_) across each time point. Provided statistical assumptions are met, our hypotheses will be tested using random regression models [72,73]. Random regression models, also known as growth models, help to attenuate the impact of random data fluctuations, thereby increasing statistical power [72,74]. The use of random regression models also accounts for data non-independence, missing data, and nonlinear changes in the outcome variables [75].

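### Covariates are chosen by testing the randomised arms for baseline differences, instead of fixing baseline VO2peak, age stratum and sex in advance

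*Protocol article*

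**What the plan says.** Protocol article, section 4.1.1 (Preliminary data analysis plan), opens the analysis with a comparison of the arms: "First, to ensure successful randomization, the two groups will be examined for homogeneity". It then turns the result into a modelling rule: "If it is determined that the groups differ significantly on any variable, we will include those variables as covariates in subsequent analyses". The variables to be tested are not listed, and the rule carries forward to all later analyses.

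The same section says "we will conduct the primary analysis on changes in fitness". Section 4.1.3 gives the model as a random regression (growth) model in which "a slope will be fitted for the outcome variable (i.e., VO_2peak_) across each time point". It names no covariates and does not say whether the arms share a baseline mean.

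Section 3.2 (Randomization) assigns participants "using stratified assignment by age (i.e., those over and under 35 years of age) and biological sex". No section states that these factors, or baseline VO2peak, will be in the model whatever the baseline tests show.

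Section 4.1 bases the sample size on a difference of 2.5 ml/kg/min, SD 6.0 at both time points, a correlation of 0.39, two-sided alpha 0.05 and 112 per group for 80% power.

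**The concern.** When assignment is random, any baseline difference between the arms is due to chance. A significant test is therefore not evidence that randomisation failed, and a non-significant one is not evidence that it worked. The test also says nothing about whether a variable predicts the outcome, which is the reason to adjust for it.

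Two consequences follow. First, the covariate set is not known until the arms have been compared. Second, the rule tends to leave out the variables that belong in the model. Age stratum and sex are balanced by the stratification, so they will rarely test as different. Baseline VO2peak is used as a covariate only in the roughly 1 trial in 20 where it happens to be imbalanced. At stake are precision that costs nothing to obtain and a clean prespecification of the headline result.

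**Working it through.** **Inputs (section 4.1):** SD 6.0 at both times, correlation r = 0.39, difference 2.5 ml/kg/min, two-sided alpha 0.05, 112 per arm.

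**1. Reproducing the plan's figure.** The SD of a change score is 6.0 × √(2 × (1 − 0.39)) = 6.0 × √1.22 = 6.627. For a difference of 2.5, the noncentral t gives 112 per arm and 80.3% power (normal approximation: 111 per arm, and 80.6% power at 112). The plan's figure is therefore a comparison of change scores without baseline adjustment.

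**2. Link to the growth model.** With three equally spaced visits and complete data, the fitted linear slope is (12-month value − baseline)/12. A growth model that leaves baseline means free by arm and has no baseline covariate thus carries the same information as the change score.

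**3. Baseline always adjusted.** The residual SD is 6.0 × √(1 − 0.39²) = 5.525. Power at 112 per arm is 92.1% (t) or 92.3% (normal), and 80% power needs 77 to 78 per arm.

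**4. The rule as written, applied to baseline VO2peak.** This was simulated with 100,000 trials of 112 per arm: test baseline VO2peak at 5%, use baseline adjustment if significant, and otherwise use the change score.

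| Analysis | Type I error | Power |
|---|---|---|
| Change score, never adjusted | 4.9% | 80.2% |
| Section 4.1.1 rule | 4.2% | 81.4% |
| Baseline always adjusted | 5.0% | 92.0% |

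The loss is 92.0 − 81.4 = 10.6 points.

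The rule's type I error can be decomposed. Baseline is significant in 4.96% of null trials, where the adjusted analysis rejects 5.3% of the time; the change score would have rejected 20.7% there. In the other 95.04% the change score rejects 4.1%. Together: 0.9504 × 4.12% + 0.0496 × 5.34% = 4.2%. The error is low because the trials in which the change score over-rejects are switched to the adjusted analysis.

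**5. Dependence on the correlation.** Section 4.1 also gives the 12-month changes as 3.5 ± 6.0 and 1.0 ± 6.0. If that 6.0 is the SD of change, then 6.0 × √(2 × (1 − r)) = 6.0 and r = 0.5.

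| r | Change score (normal) | Baseline adjusted (normal) | Loss under the rule, simulated |
|---|---|---|---|
| 0.39 | 80.6% | 92.3% | about 10 points |
| 0.5 | 87.7% | 95.0% | about 6 points |
| 0.6 | 93.7% | 97.4% | about 3 points |
| 0.7 | 98.1% | 99.2% | about 1 point |

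**6. Stratification factors.** The document does not say how much of the variance of change they explain, so the share is an assumption. At 0, 5, 10 and 20%, leaving out a balanced stratification factor gives type I error of about 4.9, 4.4, 3.9 and 2.9%, and power lower by about 0, 1, 3 and 5 points than with it included.

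**The case against.** The strongest reply is that the trial is not harmed by its own standard. The plan promises 80% power on an unadjusted change contrast and still has about 81% under the rule. The error rate is below 5%, not above it. Both points stand: this is avoidable inefficiency and a data-dependent model, not underpowering or false-positive inflation.

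A second reply is that the simulation is not the stated model. In a growth model, baseline VO2peak is always present as a response, and if the arms were given a common baseline mean most of the loss would disappear. That is right, but section 4.1.3 states no such constraint, so the figures above depend on reading the analysis as the contrast that sized the trial.

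A third reply is that covariate lists are usually left to the analysis plan, which is not shown. That would excuse silence. It does not excuse a stated selection rule, which a later plan would have to contradict.

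Four stronger readings are tempting and are not supported:

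- A reader might infer from section 2.5 that the trial will adjust for satisfaction ("Satisfaction for the assigned group (i.e., net promoter score) will be measured at the end of each month") or for post-baseline self-efficacy, although the aims include "changes in self-efficacy, blood pressure, loneliness, anxiety, and depression". The section heading covers covariates and other variables alike, and nothing says either will be adjusted for. Month-end satisfaction has no baseline value to trigger the rule.
- A reader might cite mean VO2peak of 42.1 in men and 34.2 in women (section 4.1) as evidence that sex predicts the outcome. Those are levels. A constant level difference cancels in a change score, and the document has no figure for sex and change.
- A reader might compute 1 − 0.95²⁰ = 64% as the chance of at least one significant imbalance among about 20 variables. That assumes independent tests. With an assumed common correlation of 0.2 or 0.4 it is 59% or 48%. Adding one non-prognostic covariate also costs only about 1 to 2 points of power.
- A reader might say that the whole primary model is unknown in advance. The outcome, visits and model class are stated; only the covariates are open.

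**Conclusion.** The point holds as a defect in a stated rule. Section 4.1.1 selects covariates by a test that cannot do what it is meant to do, and it tends to exclude the variables with the best claim to inclusion.

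On the plan's own inputs, the rule applied to baseline VO2peak gives about 81% power and 4.2% type I error, where routine baseline adjustment would give about 92% and 5%. This rests on complete data for 112 per arm, an unadjusted change contrast and r = 0.39. The gain shrinks as the correlation rises and would largely vanish under a common-baseline growth model. The further effect of omitting age stratum and sex cannot be sized from the document and could be nil. The trial meets its stated power either way. The case for change is that the correction is free and makes the covariate set known in advance.

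**What to change.** Delete the homogeneity test as a trigger for covariates in section 4.1.1. A descriptive baseline table can remain.

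Prespecify in its place:

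- For VO2peak, and for other outcomes measured before assignment: the baseline value of the outcome (or a longitudinal model with a common baseline mean), plus age stratum and sex.
- For outcomes with no pre-assignment value, such as attendance, injuries and enjoyment of the assigned group: age stratum and sex only.

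State in section 4.1.3 which of the two baseline treatments the growth model uses.

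The cost is about one paragraph of wording. The variables are already collected, and no participants or visits are added. The change should be made before data are examined by arm.

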### Sample size determination

4.1

Our power and sample size calculations are based on the following considerations. First, studies among untrained adults have shown that supervised group exercise can increase VO_2peak_ by approximately 4 ml/kg/min over 12 months [[64], [65], [66]]. Based on data derived from the National Health and Nutrition Examination Survey (NHANES) among men (*mean*_VO2peak_ = 42.1 ml/kg/minute) and women (*mean*_VO2peak_ = 34.2 ml/kg/minute) 30–39 years of age [67], we assume the baseline VO_2peak_ of participants will be approximately 35.0 (SD = 6.0). The SD of 6.0 is a conservative estimate using data from the Naval Research Lab, where it was 6.3 and 3.9 in men and women, respectively [68]. After 6-months, we anticipate that participants in both PlayFit and STT will improve their VO_2peak_ by approximately 10% (i.e., 3.5 ml/kg/min), owing to similar rates of program adherence. However, after 12-months, we anticipate only those randomized to PlayFit will maintain these changes in cardiorespiratory fitness, due to better program adherence. These differences in adherence will lead to a maintained improvement (versus baseline) in VO_2peak_ of PlayFit participants at 12-months of 3.5 ± 6.0 ml/kg/minute versus 1.0 ± 6.0 for STT. In this case, sample sizes of 112 in each group achieve 80% power to detect a mean difference of 2.5 ml/kg/minute with a standard deviation of 6.0 at the first time point, a standard deviation of 6.0 at the second time point, a two-sided significance level (*α*) of 0.05, and a correlation between measurements of 0.39. To account for participant attrition, we will oversample at a rate of 25%. Therefore, we will recruit up to 280 participants for the proposed study.

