#### Missing data

4.1.2

If the combined rate of missingness on a variable is less than 5%, we will not impute missing data. In the event of unanticipated higher levels of missing data, we will examine the nature of the missing values. If it is believed that variations in attrition can be explained by observed variables, these data will be considered missing at random (MAR) and no special adjustments will be necessary [70]. If, instead, we find that a portion of the variability in attrition could be explained further by unobserved variables, we will employ multiple imputation, carrying the last observation forward.

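### The no-change assumption for participants lost to follow-up contradicts the month-6 to month-12 decline on which the trial is powered, and conflicts with the other missing-data rules for VO2peak

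*Protocol article*

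**What the plan says.** Four places in the protocol article bear on missing VO2peak values.

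- **4.1 Sample size determination.** Both arms are expected to gain 3.5 ml/kg/min by month 6. Then "after 12-months, we anticipate only those randomized to PlayFit will maintain these changes in cardiorespiratory fitness", and STT drops back to +1.0. The difference of 2.5 at month 12 is the powered effect. Recruitment is raised by 25%, to 280, to allow for attrition.
- **4.1.1 Preliminary data analysis plan.** The primary outcome is analysed by intention to treat on all available data, "with the assumption that participants who are lost to follow-up will not have changed their level of fitness since their last observation". No threshold or condition is attached.
- **4.1.2 Missing data.** Nothing is imputed below 5% missing. Above that, if observed variables explain attrition, the data count as MAR and need no adjustment. If unobserved variables also play a part, "we will employ multiple imputation, carrying the last observation forward".
- **4.1.3 Analysis of main outcome.** Hypotheses are tested with growth models: "The use of random regression models also accounts for data non-independence, missing data, and nonlinear changes in the outcome variables".

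**The concern.** The trial's effect lies entirely between month 6 and month 12. An assumption that fitness stays where it was last measured removes that change for anyone whose last test was at month 6. For STT, this credits a gain that the plan says will mostly be gone.

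The rules also do not fit together. A likelihood-based growth model uses the observed visits and fills nothing in, whereas 4.1.1 fixes a value for each lost participant. Two analysts following this text could report different primary results.

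The fallback in 4.1.2 is not a coherent method. LOCF inserts one fixed value, while multiple imputation draws several to carry the uncertainty. It is also reserved for attrition that depends on unobserved variables. The observed data cannot establish that condition, and carrying a value forward does not repair it.

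The issue is not remote. Section 4.1.2 treats more than 5% missing as unexpected, yet 140 recruited for 112 needed per arm allows for 20% loss (1 − 112/140).

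**Working it through.** **Inputs from section 4.1.**
- Stated result: "sample sizes of 112 in each group achieve 80% power to detect a mean difference of 2.5 ml/kg/minute".
- SD: 6.0 at both measurements.
- Baseline to follow-up correlation: 0.39.
- Alpha: 0.05, two-sided.
- Mean changes: +3.5 in both arms at month 6; +3.5 (PlayFit) and +1.0 (STT) at month 12.

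**Reproducing the plan's figure.**
- SD of change = √(6² + 6² − 2 × 0.39 × 6 × 6) = √43.92 = 6.627.
- The normal approximation gives 111 per arm for 80% power. The noncentral t gives 79.9% at 111 and 80.3% at 112, so the stated 112 reproduces.
- 112 × 1.25 = 140 per arm, 280 in total.

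**Effect of carrying forward.** Let *a* be the fraction of an arm lost after month 6 and *b* the fraction lost before it. Then

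LOCF mean change = (1 − a − b) × (month-12 mean) + a × 3.5 + b × 0.

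With 140 per arm, the standard error of the difference is 6.627 × √(2/140) = 0.792, and power ≈ Φ(difference/0.792 − 1.96).

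The protocol gives neither the timing nor the arm of loss, so every loss pattern below is an assumption.

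*Those lost follow their own arm's expected course (true difference 2.5):*

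| Loss, PlayFit / STT | PlayFit | STT | Difference | Power |
|---|---|---|---|---|
| 5% / 5%, after month 6 | 3.5 | 0.95×1.0 + 0.05×3.5 = 1.125 | 2.375 | 85% |
| 20% / 20%, after | 3.5 | 0.8×1.0 + 0.2×3.5 = 1.5 | 2.0 | 71% |
| 10% / 30%, after | 3.5 | 0.7×1.0 + 0.3×3.5 = 1.75 | 1.75 | 60% |
| 30% / 10%, after | 3.5 | 0.9×1.0 + 0.1×3.5 = 1.25 | 2.25 | 81% |
| 20% / 20%, before | 0.8×3.5 = 2.8 | 0.8×1.0 = 0.8 | 2.0 | 71% |
| 10% / 30%, before | 0.9×3.5 = 3.15 | 0.7×1.0 = 0.7 | 2.45 | 87% |

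For loss after month 6, the shrinkage is 2.5 × the STT fraction lost. At a difference of 2.0, 173 per arm would be needed for 80% power.

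A simulation (4,000 trials, correlation of 0.39 assumed between all visits) gave, under LOCF after month 6, 2.01 and 71% for 20%/20%, 1.72 and 58% for 10%/30%, and 2.26 and 81% for 30%/10%. With 20% loss per arm unrelated to outcome and no carry-forward, it gave 2.51 and 80%.

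*Those lost after month 6 return to baseline, and completers keep 3.5 and 1.0:*

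| Loss, PlayFit / STT | True difference | LOCF | LOCF bias | Observed data only | Its bias |
|---|---|---|---|---|---|
| 20% / 20% | 2.8 − 0.8 = 2.0 | 2.0 | 0 | 2.5 | +0.50 |
| 10% / 30% | 3.15 − 0.7 = 2.45 | 1.75 | −0.70 | 2.5 | +0.05 |
| 30% / 10% | 2.45 − 0.9 = 1.55 | 2.25 | +0.70 | 2.5 | +0.95 |

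**The case against.** Several stronger readings are tempting, and the protocol does not support them.

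- **That LOCF is plainly the primary analysis.** Section 4.1.1 also says all available data are used and states an assumption, not an imputation step. Section 4.1.2 names carry-forward only in one branch, and 4.1.3 relies on a model that accommodates missing visits. What the text establishes is a contradiction between sections, one side of which is LOCF. This objection stands, but nothing withdraws the 4.1.1 assumption.
- **That the decline is assumed away for everyone who quits.** Section 4.1 attributes the STT decline to poorer adherence, which means session attendance. Someone who stops attending but takes the month-12 test is observed. Only those lost after month 6 are affected. Nor does the plan predict higher loss in STT: it predicts lower adherence and applies the same attrition allowance to both arms.
- **That the bias always dilutes PlayFit's advantage.** It does so if those lost follow their arm's course. If they return to baseline, the bias may be zero or may favour PlayFit.
- **That the trial has 60% or 71% power.** These figures are for a two-group change-score test under assumed losses, whereas the planned model uses three visits. Some scenarios stay above 80%.
- **That dropping LOCF restores 2.5 at 80% power.** This holds only when the 20% loss is unrelated to outcome. In the return-to-baseline table, the observed-data result is further from the truth than LOCF in two of three cases.
- **That the missing sensitivity analysis is itself a defect.** An article may leave that to the analysis plan. The defect is the fallback that 4.1.2 does state.

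**Conclusion.** The point holds. For participants lost after month 6, the no-change assumption for VO2peak contradicts the STT fall of 2.5 ml/kg/min (3.5 − 1.0) that constitutes the whole powered effect. It is unreconciled with 4.1.2 and 4.1.3, and the 4.1.2 fallback joins two incompatible methods.

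The size is conditional. On the plan's own means, with losses after month 6 that follow each arm's course, the month-12 difference ranges from 2.375 (5% per arm) to 1.75 (PlayFit 10%, STT 30%). If those lost return to baseline, the bias ranges from −0.70 to +0.70 across the scenarios examined. LOCF therefore cannot be defended as reliably conservative, and neither its direction nor its size can be predicted from the document. Because the rule bears on the primary contrast, it should be settled before outcome data are analysed.

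**What to change.** 1. In 4.1.1, delete the assumption of no change since the last observation. Keep the commitment to all available data.
2. In 4.1.2, delete the rule that combines multiple imputation with carry-forward.
3. In 4.1.3, name a single primary analysis: a likelihood-based repeated-measures model on all observed VO2peak values under MAR, which estimates the month-12 contrast between arms (for example, with visit as a category).
4. MAR does not cure dropout that depends on the unseen outcome. Replace the 4.1.2 fallback with a multiple-imputation sensitivity analysis, delta-adjusted or return-to-baseline, for participants lost to follow-up. It should always be run, not triggered by a judgement on why data are missing.

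The cost is a change of wording and one extra analysis. No new data and no change in sample size are needed for this point.
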